Pulse wave measurements are performed by the same, trained observer in the morning under standardized conditions. Before performing the actual measurements, marks are made on the skin of the patient over the part of the a. radialis, a. carotis, and a. femoralis where the pulse is most prominent. The suprasternal notch (SN) is used as reference point and is also marked. A tape measure is used to measure the distances between the SN and a. radialis, carotid artery and a. femoralis, respectively. Patients are then requested to rest in the supine position, in a quiet room of constant temperature for 10 minutes. The measurements are all undertaken on the right side. Patients have to be in the fasting state and have to refrain from smoking 8 hours before examination. Diabetics are allowed a light meal and all participants are allowed a glass of water. All medications including study medication are to be taken after examination. Quality of the measurements is evaluated partly by a visually acceptable curve of the peripheral pulse wave and partly by a maximum difference between 2 successive measurements of ≤7% and an average height of the wave of > 80 mV(42). Pulse wave measurements are done in two sets. The first is the pulse wave (PW) and after this the PWV. The AIx is derived from the PW. It is calculated as the percentage of augmentation (AG) of the pulse pressure (PP). On the recordings of the peripheral waves the PP, the first peak of the pulse wave (P1) and the second peak (P2) are marked. The augmentation is the difference between P1 and P2. And the AIx is this difference taken out of the PP. These calculations are all performed automatically by the SphygmoCor software. An acceptable Quality Index (QI) is > 80%. QI is calculated by the software from the other stated quality indicators (pulse height, max. 7 % difference between two measurements).

*Ambulatory blood pressure measurements*

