AMBPs are automatically measured blood pressures during ordinary daily activities for a time period of approximately 24 hours. AMBP has been found reproducible in population studies (25-30), hypertensive populations (46) and diabetics (47). The reproducibility of AASI has been proven less reliable in an essentially hypertensive population (48) . The brachial BP is measured in the office using the ABPM equipment on the non-dominant arm. After manual measurements the apparatus will automatically measure the BP every 15 minutes in daytime, which is defined from 7 am until 11 pm. Hereafter the measurements will be performed every 30 minutes from 11 pm till 7 am (49). All patients receive a diary in which they are to make notes of physical activity, meals and rest as well as bedtime and rising time in the morning. For calculation of AASI a minimum of 21 readings of BP is required. These must be spread out over the whole period with at least 7 successful readings during night time. AASI is calculated in the following manner: (1-(the slope of diastolic BP/slope of systolic BP)). It follows that the stiffer the arterial tree, the more the regression line will go towards 0 and AASI thus towards 1. Previous studies have provided references for AASI in the background population. AASI for normotensive individuals is 0.57. In younger individuals AASI is 0.53 increasing to 0.72 in the elderly (30).

*Intervention – study medication*

The study medication is eplerenone, a selective aldosterone receptor antagonist. It is an approved drug, which in this study will be used on a non-appraised indication. The Summaries of Product Characteristics (SPC) in Danish will be used as reference document for evaluation of possible side effects and will be accessible at the site of investigation when the study is initiated.

Initial recommended dose is 25 mg once daily. The dose will be increased to 50 mg eplerenone in once daily dosing after 1 week. In this study eplerenone will be added to the study participants’ usual medication. The manufacturing company Pfizer Aps has been informed of the study.

*Control*

The control group will continue their usual medical therapy.

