### 3.13 Practical performance of study

Patients who fulfil the inclusion criteria and who are interested in participating in the study are informed about the study. The written information is handed out and will be thoroughly explained. A form of written informed consent is to be signed by the patient and the informant/investigator. If consent is given, dates for the study days will be given.

Demographic data will be registered.

Randomization: When inclusion criteria are met including the performance of a screening for PW measurements and the run-in period has been completed, patients are randomized to the active treatment arm with eplerenone or the control arm for 24 weeks.

Planning:

A deviation of ± 1 week from the initially planned date for visits is permitted. Collection of 24 hour urine is allowed for at time deviation of ± 3 days with respect to blood sampling. Participants’ visits are planned to be identical in both groups.

Visits are planned as shown below:

| ***Visit number*** | ***Time with reference to inclusion for the individual patient*** | ***Purpose of visit*** | ***Estimated time used for the visit*** |
| --- | --- | --- | --- |
|  | Screening | signing of written informed consent, PW measurement test, ECG, blood sampling, demographic data noted | 1-1½ hours |
| 1a | Week 1 | randomization, PW measurement, AMBP, blood sampling, 24 h urine, study medication handed out | 1 hour |
| 1b | Week 1 | return of AMBP device | 10 minutes |
| 2 | Week 2 | blood sampling, BP, increase in study medication | 30 minutes |
| 3 | Week 4 | blood sampling, BP, study medication handed out | 30 minutes |
| 4 | Week 8 | blood sampling, BP, study medication handed out | 30 minutes |
| 5a | Week 12 | PW measurement, AMBP, blood sampling, 24 h urine, study medication handed out | 1 hour |
| 5b | Week 12 | return of AMBP device | 10 minutes |
| 6 | Week 16 | blood sampling, BP, study medication handed out | 30 minutes |
| 7 | Week 20 | blood sampling, BP, study medication handed out | 30 minutes |
| 8a | Week 24 | PW measurement, AMBP, blood sampling, 24 h urine, study medication and packages returned | 1-1½ hours |
| 8b | Week 24 | return of AMBP device | 10 minutes |

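### The baseline 24-hour blood pressure recording runs after drug hand-out and the final one after drug return, with nothing to keep the first drug-free or the last on treatment

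*Protocol*

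**What the plan says.** The visit table in Protocol section 3.13 gives visit 1a (week 1) as "randomization, PW measurement, AMBP, blood sampling, 24 h urine, study medication handed out" and visit 8a (week 24) as "PW measurement, AMBP, blood sampling, 24 h urine, study medication and packages returned". Visits 1b and 8b each have one purpose: "return of AMBP device". At visit 5a (week 12) medication is handed out and none is returned.

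Section 3.4 says of the recording: "AMBPs are automatically measured blood pressures during ordinary daily activities for a time period of approximately 24 hours". On dosing on pulse wave days it says: "All medications including study medication are to be taken after examination". On titration it says: "The dose will be increased to 50 mg eplerenone in once daily dosing after 1 week"; the table in 3.13 places the increase at visit 2, week 2.

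On urine, section 3.13 says: "Collection of 24 hour urine is allowed for at time deviation of ± 3 days with respect to blood sampling".

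Section 3.5 puts randomisation after consent and the run-in and does not mention the baseline measurements. Controls stay on their usual therapy (section 3.4), so there is no placebo. PWV is primary; AASI, blood pressure and albuminuria are secondary (section 3.3). AASI is the only secondary question named in the aim (section 3.1).

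**The concern.** A change from baseline is interpretable only if baseline is untreated and the endpoint is on treatment. The AMBP schedule secures neither. The baseline recording begins at the visit where eplerenone patients receive their tablets, and the final recording begins at the visit where they give them back. If a first dose falls inside the baseline recording, or the last dose precedes the final recording by more than a dosing interval, the apparent change in AASI and ambulatory blood pressure shrinks, and only in the eplerenone arm. Since week 12 is recorded on treatment, a final recording off treatment could also look like a fading effect between weeks 12 and 24.

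The urine window allows the same mistiming of albuminuria. Separately, randomisation is listed ahead of the baseline pulse wave measurement, and no section requires that measurement to be finished before the allocation is known.

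**Working it through.** **The plan's own figure.** The only computed design figure is the sample size for PWV: difference 1, SD 1.5, two-sided 0.05, power 0.8 (Statistics section). A two-sample t calculation gives 36.3057 per group, against the stated 36.3058. Power is 0.808 with 37 and 0.838 with 40 per group. The figure is correct and this point does not touch it. No figure is given for AASI, ambulatory pressure or albuminuria.

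**How much of the recording falls after the visit.** Section 3.4 schedules readings every 15 minutes from 7 am to 11 pm and every 30 minutes overnight: 16 × 4 + 8 × 2 = 80 readings. Visit 1a is planned at 1 hour and 8a at 1 to 1½ hours, so nearly all readings come after the patient leaves. AASI also needs at least 7 night readings, which must come after the visit. Restricting the analysis to readings taken during the visit is therefore not possible.

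**Dose timing.** If the increase comes one week after the first dose and takes place at visit 2, the first dose is at about visit 1. No section says whether a dose is taken on the day of 1a, or on the day of 8a before the tablets go back. Let *f* be the share of the full effect present during the baseline recording if a first dose is taken that day. Let *g* be the share remaining during the final recording if no dose is taken that day. The four possibilities are:

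| Dose on day of 1a | Dose on day of 8a | Baseline recording | Final recording | Share of effect in the week-24 change |
|---|---|---|---|---|
| yes | yes | first dosing day | on treatment | 1 − f |
| no | no | drug-free | past the last dosing interval | g |
| yes | no | first dosing day | past the last dosing interval | g − f |
| no | yes | drug-free | on treatment | 1 |

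If the visit-day rule is the same at both ends (rows 1 and 2), one recording is out of line. Only the last row aligns both, and no section states it.

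**Illustrative size (assumptions only).** The documents give no onset or carry-over figure. Taking f from 0 to 0.3 and g from 0.5 to 1.0:

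- 1 − f runs from 0.70 to 1.00.
- g runs from 0.50 to 1.00.
- g − f runs from 0.5 − 0.3 = 0.20 to 1.0 − 0 = 1.00.

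Each range includes no loss. In a comparison of week-24 values between arms, f drops out and only g matters.

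For a hypothetical secondary endpoint with the PWV standardised effect (1/1.5 = 0.667) and 40 per group, a lost share *a* multiplies the required number by 1/(1 − a)²:

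| Lost share a | Power | Required number, multiple |
|---|---|---|
| 0 | 0.838 | 1 |
| 0.10 | 0.755 | 1.23 |
| 0.20 | 0.654 | 1.56 |
| 0.30 | 0.540 | 2.04 |
| 0.50 | 0.313 | 4.0 |

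**PWV.** Section 3.4 has study medication taken after the pulse wave examination. At 1a PWV is therefore pre-dose, and at 5a and 8a it is measured before that day's dose. Exposure is as intended at all three visits.

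**Urine.** Blood is sampled at 1a and 8a. Three days either way allows collection before 1a (drug-free) or after the first dose, and before 8a (on drug) or after drug return.

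**The case against.** The strongest reply is that the documents are silent on dose days, and silence is not a wrong schedule. The sentence that places dosing after the examination could equally let a patient take a dose at 8a and then hand back the remaining tablets. The final recording would then cover an ordinary dosing interval. This stands. A reader might infer that the final recording covers 24 to 48 hours after the last dose, but that is one possibility and not something the protocol states. The reply does not clear the schedule, because the same reading puts the first dose inside the baseline recording.

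Three other stronger readings also fail:

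- **PWV measured at the wrong exposure.** A reader might infer this from the visit 1a entry. The dosing sentence rules it out.
- **Albuminuria mistimed at both ends.** The window permits this but equally permits correct timing.
- **Baseline PWV taken with the allocation known.** The entry for 1a is a list of purposes, not a sequence: it places a 24-hour urine collection in a one-hour visit. The protocol also limits observer discretion through a maximum 7% difference between successive measurements and a quality index above 80%. What stands is that nothing requires the measurement to come first.

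It is also fair to say that the endpoints affected by exposure are secondary, that any distortion is toward no effect, and that the initial 25 mg dose makes a large first-day effect harder to assume.

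**Conclusion.** The point holds for the two AMBP recordings. As scheduled, the baseline recording runs after randomisation and hand-out, the final one runs after drug return, and no section keeps the first drug-free or the last on treatment. Any mismatch falls only on the eplerenone arm and would shrink the apparent change in AASI and ambulatory blood pressure, assuming the drug has an effect to lose. The size cannot be derived from the documents; the shares and powers above rest on assumed values and include no loss at all.

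For albuminuria the fault is a window that is not tied to allocation or drug return. For PWV, exposure and power are not affected; the remaining point is the missing requirement that baseline be completed before allocation is known. The change is worth making because analysis cannot recover a mistimed 24-hour recording and the correction needs no new visit.

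**What to change.** - In sections 3.5 and 3.13, state that the baseline pulse wave measurement, AMBP and 24-hour urine are completed before the randomisation envelope is opened, for example by using the existing visit 1b.
- Reconcile sections 3.4 and 3.13 so that the final AMBP and urine collection are completed before study medication is returned, for example by using the existing visit 8b.
- Limit the urine window so that collection falls before allocation at visit 1 and before drug return at visit 8.

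The cost is somewhat longer visits at 1b and 8b, now planned at 10 minutes each. No dosing rule is proposed: the sponsor must reconcile the timing of the first and last dose with the measurement schedule.

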## Procedure for termination of the study

Personal data will be stored for 10 years. It will be destroyed after this. Data will be kept in the Department of Nephrology at Herlev Hospital. Participant’ personal information will be treated with the confidentiality required by the Danish Data Protection Agency (Datatilsynet).

## Statistics

Power calculations have been made based on a minimal clinically relevant difference on the primary end point PWV of 1 m/s. It has been shown that an increase of PWV of this size increases mortality by 39%(19).

From our own data we have a standard deviation of 1.5 on PWV. At a level of significance of 0.05 and power 0.8 a calculation of number of participants for each group should reach 37. We plan to include 40 patients in each group.

Two-sample t test power calculation

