**n = 36.3058**

delta = 1

sd = 1.5

sig.level = 0.05

power = 0.8

alternative = two.sided

NOTE: n is number in *each* group

Patients who are with drawn are not replaced.

Differences in PWV will be statistically examined using paired t tests.

The secondary effect parameters will also be examined using this statistic method. For the groups as a whole two sample t test will be applied. If data do not fit the normal distribution they will be transformed.

1. ***Quality control***

Normal procedures for quality control will be followed, see ICH GCP Guidelines. Data will be monitored by The GCP unit at Copenhagen University Hospital, Bispebjerg Hospital, [name], [name], [name]. As informed consent is given, a permission from the participant for the Danish Medicines Agency and the GCP unit to have access to the patient’s hospital medical files will be sought. A copy of the text is available (in Danish).

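### The only stated between-group test of PWV is a two-sample t test with no baseline covariate, although baseline PWV is scheduled for every patient, and the SD of 1.5 is not tied to the variable tested

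*Protocol*

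**What the plan says.** The Statistics section starts from a "minimal clinically relevant difference on the primary end point PWV of 1 m/s" and continues: "From our own data we have a standard deviation of 1.5 on PWV". The calculation is labelled "Two-sample t test power calculation", with "alternative = two.sided" in the printed output and "At a level of significance of 0.05 and power 0.8" in the text. The output gives 36.3058 per group. The text raises this to 37 and then states: "We plan to include 40 patients in each group".

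For analysis, the same section assigns paired t tests to differences in PWV and to the secondary parameters. The between-group method is one sentence: "For the groups as a whole two sample t test will be applied". It does not say whether PWV at follow-up or change from baseline enters that test, and it names no covariate.

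Section 3.3 defines the primary endpoint as a difference in PWV, without a time point and without saying whether the difference is between arms or between visits. The visit table in section 3.13 lists for visit 1a: "randomization, PW measurement, AMBP, blood sampling, 24 h urine, study medication handed out". PWV is measured again at weeks 12 and 24.

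**The concern.** PWV varies between patients for lasting reasons. The Background names age, blood pressure and diabetes as independent influences. A baseline value carries part of that variation, and this trial collects it from everyone before treatment starts. A test on follow-up levels alone discards it. A test on changes uses it, but with a fixed weight of one whatever the correlation between the two measurements. A linear model with baseline as covariate estimates the weight. With 40 patients per arm and no stratification described in section 3.5, the gain is worth having.

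The second issue is that the SD and the test cannot be matched. The SD of a single PWV and the SD of a within-patient change are equal only when the correlation is 0.5 (taking equal variances at the two times). Since the protocol states neither which SD it has nor which variable it tests, a reader cannot confirm that the stated power belongs to the stated test.

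**Working it through.** **Inputs from the protocol (Statistics):** difference 1 m/s, SD 1.5, two-sided 0.05, power 0.80, 40 per arm planned.

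**Assumption:** the correlation rho between visit 1a PWV and follow-up PWV. The protocol does not give it, so a range is shown. Equal variance at the two times and full completion are also assumed.

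**Step 1: the plan's own figure.** A two-sample t test (noncentral t) with standardised difference 1/1.5 = 0.667 needs n = 36.306 per arm, rounded up to 37. This reproduces the printed output. Power is 0.808 at 37 per arm and 0.838 at 40.

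**Step 2: if 1.5 is the SD of PWV levels.**

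- SD of change = 1.5 × √(2(1 − rho)). At rho 0.3 this is 1.5 × √1.4 = 1.775; at 0.5, 1.5; at 0.7, 1.5 × √0.6 = 1.162.
- Residual SD after baseline adjustment = 1.5 × √(1 − rho²). At rho 0.3 this is 1.5 × √0.91 = 1.431; at 0.5, 1.299; at 0.7, 1.5 × √0.51 = 1.071.

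Power at 40 per arm:

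| rho | Follow-up levels | Changes | Baseline-adjusted |
| --- | --- | --- | --- |
| 0.3 | 0.838 | 0.701 | 0.870 |
| 0.5 | 0.838 | 0.838 | 0.925 |
| 0.7 | 0.838 | 0.967 | 0.985 |

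The adjusted figures use the same t calculation with the smaller SD. The one degree of freedom spent on the covariate (77 instead of 78) is ignored.

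Change-score power stays at or above 0.80 at 40 per arm for every rho from about 0.45 upwards.

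**Step 3: if 1.5 is the SD of change.** The level SD is then 1.5/√(2(1 − rho)): 1.268, 1.5 and 1.936 at rho 0.3, 0.5 and 0.7.

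| rho | Follow-up levels | Changes | Baseline-adjusted |
| --- | --- | --- | --- |
| 0.3 | 0.936 | 0.838 | 0.955 |
| 0.5 | 0.838 | 0.838 | 0.925 |
| 0.7 | 0.626 | 0.838 | 0.891 |

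**Step 4: why the ordering is general.** The variance of the adjusted comparison relative to follow-up levels is 1 − rho², that is 0.91, 0.75 and 0.51 at the three correlations. Relative to changes it is (1 − rho²)/(2(1 − rho)) = (1 + rho)/2, that is 0.65, 0.75 and 0.85. Neither ratio exceeds 1, so adjustment is at least as precise as either t test at any rho, apart from the one degree of freedom.

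**The case against.** The strongest reply is that nothing here is an error. A two-sample t test in a randomised trial is valid. Chance baseline imbalance adds variance, which the standard error already reflects, and does not bias the estimate. The sample size reproduces. If the SD is read in the plainest way, as the SD of PWV levels, the power is right for a follow-up comparison and conservative for an adjusted one. Covariate adjustment is also often settled in a statistical analysis plan, which may exist. All of this stands, and it limits the point.

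A reader might infer that the trial is underpowered. The protocol does not support that. Power at 40 per arm falls below 0.80 only in mismatched cases: a level SD with changes tested and rho below about 0.45, or a change SD with levels tested and rho above a value between 0.5 and 0.6. Neither case is documented. The standardised conditions and single trained observer in section 3.4 do not fix the 24-week correlation, but they give no reason to expect a low one.

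A reader might also infer that the between-group test ignores baseline. That is not established either. The endpoint is called a difference and the text speaks of differences in PWV, so a test on changes, which uses baseline, is a natural reading.

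The gain also depends on which t test is meant. Against changes it is small when rho is high (0.985 against 0.967 at rho 0.7). Against levels it is small when rho is low (0.870 against 0.838 at rho 0.3). The large gains at opposite ends of the range cannot both apply.

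The reply does not remove the precision argument. The protocol is not silent on method: it fixes a t test without a covariate. A better method is available from data already scheduled. Nor can a later analysis plan alter the SD on which 40 per arm was based.

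**Conclusion.** The point holds as a free improvement together with a needed clarification. The stated between-group test is unadjusted although baseline PWV is planned for everyone. Replacing it with a baseline-adjusted comparison loses nothing beyond one degree of freedom. With 1.5 as the SD of levels and 40 per arm, adjusted power is 0.870 to 0.985 over assumed correlations of 0.3 to 0.7, against 0.838 for levels and 0.701 to 0.967 for changes. If 1.5 is instead the SD of change, adjusted power is 0.955 to 0.891 over the same range, so the adjusted analysis stays above 0.80 under either meaning of the SD.

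The stated 80% is correct when 1.5 is the SD of the variable tested. What the protocol leaves open is whether that condition is met. The size of the gain rests on an assumed correlation and on full completion. If three patients per arm were lost (37 left, level SD), the adjusted figures would be 0.843, 0.904 and 0.977.

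**What to change.** In the Statistics section, make the primary between-group analysis a linear model of end-of-treatment PWV on treatment arm with visit 1a PWV as covariate, and report the adjusted difference with its 95% CI. Week 24 is the end of the randomised period and the obvious candidate, but section 3.3 names no time point, so the sponsor should confirm it as primary.

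In the same section, say whether 1.5 is the between-patient SD of PWV or the SD of within-patient change. Give the baseline to follow-up correlation if the investigators' own data provide it, and restate power for the adjusted analysis. Keep 40 per arm.

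The cost is protocol wording. No extra patients, visits or measurements are needed.
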